### Control group

Participants in the control group will not receive any interventions during the 12-week study period.

### Outcome measures

Baseline descriptive data including age, gender, date of surgery, surgical procedure performed, and the knee undergoing surgery will be obtained by questionnaire and from surgical records. Radiographic disease severity will be assessed from the screening x-ray using the Kellgren and Lawrence grading system [47]. Height and body mass will be measured. For a summary of all measures collected in the study see Table 2.

**Table 2 T2:** Outcome measures summary

**Primary outcome measures**	
Peak external knee adduction moment during stance	a) Walking (normal pace)
	b) One-leg rise
**Secondary outcome measures**	
Peak external knee adduction moment during stance	a) Walking (fast pace)
	b) One-leg hop for distance
External knee adduction moment impulse during stance	a) Walking (normal pace and fast pace)
	b) One-leg rise
	c) One-leg hop for distance
Knee and hip muscle strength	Isometric and isokinetic knee extensors and flexors (isokinetic dynamometer)
	Isometric hip abductors and hip adductors (instrumented manual muscle tester)
Muscle activity patterns and co-contractions	Surface electromyography
Objective functional performance	a) One-leg rise
	b) Knee bends
	c) One-leg hop for distance
Pain, other symptoms, function in ADL and Sport and Recreation, quality of life	Knee injury and osteoarthritis outcome score
**Other measures**	
Peak external knee flexion moment	3-dimensional movement analysis
Dynamic tibial alignment, lateral trunk lean angle, internal foot rotation angle	3-dimensional movement analysis
Static alignment	Inclinometer
Disease severity	X-ray (baseline)
Physical activity levels	Lower Extremity Activity Scale
Adverse events	Participant log-book (follow-up)
Adherence to exercise program	Participant log-book (follow-up)
Treatment session attendance	Therapist treatment records (intervention group only) (follow-up)

All measures are obtained at baseline and 13 weeks, unless otherwise indicated.

### External knee adduction moment

Three-dimensional movement analysis will be used to assess participant’s movement as they perform three different tasks wearing standardised footwear (Dunlop Volley, Pacific Brands, Australia): i) walking (normal and fast pace), ii) one-leg rise and iii) one-leg hop for distance. Kinematic and kinetic data will be recorded using a 12-camera motion analysis system (Vicon MX, Oxford, UK) and three force plates (AMTI, MA, USA). Participants will be assessed while walking at two speeds: a normal pace walk described to participants as ‘the pace you would walk normally’ and a fast pace walk described as ‘the pace you would walk in a hurry’. Walking speed will be monitored, and six successful trials for normal and fast pace (defined as a complete foot strike on a single force plate) will be collected for each leg. At follow-up, if the average walking speed of the six trials for either normal pace or fast pace walking is outside a ±5% range from baseline walking speed, participants will be asked to adjust their walking speed accordingly. This is to ensure that six trials are collected within 5% of baseline walking speed.

For the one-leg rise task, participants will be seated in a standardised position with a chair height of 48cm, seat depth of 75% thigh length and 100° knee flexion. Participants will be instructed to flex the non-test knee holding the leg off the ground throughout the task, and rise from the seat using the test leg (leg being assessed) until standing upright, and then return to the seated position. If participants cannot rise from the seat, the chair height will be increased in increments of 2.5cm until the task can be achieved. Following two practice trials, three trials will be recorded and averaged for each leg. For the one-leg hop for distance task, participants will be instructed to stand on one foot with their arms across their chest and instructed to jump as far forward as possible and land steadily, without over-balancing on the same foot. Following, two practice trials at submaximal effort, three maximum trials where a complete foot lands on a single force plate will be averaged and collected for each leg. In an effort to minimise fatigue, three trials are considered adequate to assess the more demanding tasks (one-leg rise and one-leg hop). Reflective markers will be placed on the participant according to the University of Western Australia (UWA) marker set [54]. Data from the reflective markers (sample rate 120Hz) and ground reaction forces (sample rate 1200Hz) will be used to calculate external joint moments via inverse dynamics (Besier et al., 2003). The primary variables of interest are the peak external KAM (Nm/(BWxHT) %) and KAM impulse (Nm.s/(BWxHT) %), both normalised for body weight times height. The test-retest reliability of the UWA model for the external frontal plane moment curve during walking is 0.75 (coefficient of multiple determination, *r*^
*2*
^) [55]. Additional outcome measures that can influence the KAM during the stance phase will also be assessed, including frontal plane alignment of the tibia, peak external knee flexion moment, trunk lean in the frontal plane and internal foot rotation.

### Muscle strength

Isometric and isokinetic knee muscle strength and isometric hip abductor and adductor strength will be assessed on the previously operated leg. Maximal isometric quadriceps and hamstring strength will be measured at 60° knee flexion using a dynamometer (Humac NORM, CSMI, Massachusetts, USA). Participants will be secured in a standardised seated position. For knee strength assessment, participants will perform two sub-maximal efforts, followed by 3 maximal isometric contractions for 5 seconds each, and separated by 40 seconds rest. The maximum of 3 trials will be used for analysis. Following sub-maximal isokinetic practice efforts, maximal concentric isokinetic quadriceps and hamstring strength at 60°/sec will be measured with the participant performing 5 maximal efforts. The test-re test reliability for isometric knee strength in our laboratory for knee OA individuals is ICC 0.93.

Maximal isometric hip abductor and adductor torque will be measured using a hand-held dynamometer (Lafayette MMT 01163, Lafayette Instruments, IN, USA). For these hip strength assessments, participants will be positioned in supine with the study limb in slight abduction with no hip or knee flexion and with the pelvis and contralateral limb stabilised (Pua et al., 2008). The dynamometer will be placed over the lateral and medial femoral condyles for the hip abduction and adduction efforts, respectively. After a single sub-maximal attempt participants, will be instructed to perform two maximal trials each of 3 seconds duration, separated by 40 seconds of rest. For the hip strength assessments, the mean of two maximal trials will be used in the analysis. The reliability for hip abductor strength in our laboratory for hip OA individuals is excellent (ICC 0.84; 95% CI 0.55-0.94) [56]. For hip adductor strength, reliability in healthy individuals is ICC 0.78 (95% CI; 0.30-0.95) albeit, a slight variation on the method used in the current study [57]. All participants will receive strong standardised verbal encouragement to give their best effort during maximal trials. All strength data will be reported as torque normalised to body mass (Nm/kg).

### Muscle co-contraction and activation patterns

Muscle activity will be recorded during walking, one-leg rise and hop for distance trials using surface electromyography (EMG) sampled synchronously with kinematic data via a telemetered Noraxon Telemyo 900 system (Noraxon, AZ, USA). Surface electrodes will be placed unilaterally on the gluteus medius, quadriceps (vastus lateralis and medialis, rectus femoris), hamstrings (biceps femoris and semimembranosus) and medial and lateral gastrocnemius of the APM leg. EMG recordings during maximal isometric knee flexion, knee extension, hip abduction and plantar flexion will be used to normalise EMG data during walking, one-leg rise and hop for distance tasks. Total activation and relative activation of individual and grouped muscles will be investigated.

### Objective measures of function

Functional tests will be performed for each leg and will include the i) 30 second one-leg rise test; ii) 30-second knee bend test, and iii) one-leg hop for distance test. For the one-leg rise test, participants will sit in a standardised seated position (as described above). Participants will flex the non-test leg and rise from the seat using the test leg until standing upright and return to the seated position as quickly as possible. The number of successful, controlled one-leg rises from the chair during 30-seconds will be counted. The 30-second knee bend test assesses endurance of the hip and knee extensors. Participants will begin the test in a standardised position in single-leg standing, with the long axis of the foot aligned to a vertical line with toes placed perpendicularly. Participants will be instructed to bend the knee without bending at the hip, until the toes can no longer be seen and return to an upright position as quickly as possible [58]. The maximum number of complete repetitions performed in 30 seconds will be recorded. The one-leg hop test gives an indication of how much confidence the participant has in their knee [59] and will be administered as above. The distance will be measured from the toe of the starting position to the heel of the landing position. The farthest distance over three maximal attempts will be recorded. The 30-second knee bend test has been found to be reliable in meniscectomy patients (ICC 0.92 CI 95% 0.86-0.96) while variations of the one-leg rise test (ICC 0.84 CI 95% 0.69-0.92) and one-hop rise test (ICC 0.93 CI 95% 0.87-0.97) have also been found to be reliable in meniscectomy patients [58].

### Self-reported measures

Self-reported knee pain, other symptoms, ADL function, sport and recreation function and knee-related quality of life will be measured with the Knee Injury Osteoarthritis Outcome Score (KOOS). The KOOS consists of 42 items where each item has 5 possible answers (0–4), normalised to a score of 100, where lower score indicate worse symptoms. It has been shown to be valid and reliable in meniscectomised patients [60,61]. At the follow-up assessment, participants will rate their pain severity out of 10 on an 11-point numerical rating scale and their perceived change in physical function over the 12-week period (compared to baseline) on a seven-point ordinal scale (1-much worse to 7-much better). Also, at follow-up, participants will be questioned about their physiotherapy treatment experience.

### Other measures

A clinical measure of static knee alignment will be taken using an inclinometer [62]. Participants will be asked to stand comfortably, after which the tibial angle will be measured with respect to the vertical. This measure has been shown to be reliable (ICC = 0.94) and valid in relation to mechanical axis from full-length radiographs (r = 0.80) [62]. Physical activity will be measured using the Lower Extremity Activity Scale (LEAS), which will provide a global indication of physical activity level. From a series of options, participants select one option that best describes their current physical activity level. The LEAS is used in OA populations and has been found to be reliable and valid [63]. Participant adherence to the neuromuscular exercise program will be obtained by recording the number of physiotherapy sessions attended (out of a maximum number of eight). Participants will maintain a logbook to record the number of home exercises completed during the 12-week intervention period. For the purpose of this study, we will consider good adherence as: 1) at least 80% of physiotherapy sessions attended (i.e. 6 physiotherapy visits) and 2) at least 80% of the training sessions completed (i.e. 29 training sessions). Physiotherapists will also indicate their perceived impression of the participant’s overall adherence to the treatment on an 11-point numeric rating scale, with 0 representing ‘not at all and 10 being ‘completely as instructed’ [64].

### Sample size

A sample size of 62 participants ensures adequate power to detect significant changes in the external peak KAM and KAM impulse after the 12-week study period. As previously mentioned, a 14% reduction in peak KAM has been reported during one-leg rise in an uncontrolled study of people with knee OA following a neuromuscular exercise program [36]. Importantly, this reduction in peak KAM may be clinically relevant as it potentially corresponds to an approximate 2-fold reduction in risk of OA disease progression [25]. Therefore, we anticipate that a minimum 10% reduction in the peak KAM may be feasible with our neuromuscular program and that such a change may be potentially clinically meaningful. We anticipate that the peak KAM will remain unchanged in our control group participants. Based on our previous peak KAM data from APM participants [65], a 10% reduction equates to an absolute change of approximately 0.2 Nm/(BWxHT)%. Cautious estimates of the standard deviation of change scores are 0.3 Nm/(BWxHT)%, based on knee OA data from our laboratory investigating conservative treatments for knee OA [33]. Despite little being known about the clinically meaningful difference for KAM impulse or the response to interventions, we speculate a 10% change in KAM impulse is also feasible and potentially clinically meaningful following a neuromuscular intervention. We also anticipate that the KAM impulse will remain unchanged in our control group participants. Based on our previous KAM impulse data from APM participants [65], a 10% reduction equates to an absolute change of approximately 0.09 Nm.s/(BWxHT)%. Estimates of the standard deviation of change scores are 0.10 Nm.s/(BWxHT)% based on APM data from our laboratory where KAM impulse did not change over 2 years [65]. Therefore, a total of 27 participants per group is required to detect our anticipated changes in peak KAM and KAM impulse (assuming standard deviations as stated above) between the groups with 80% power (2 sided test, alpha=0.05). To account for 15% attrition, we will recruit 31 participants per group.

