**Methods/design:**

62 people aged 30–50 years who have undergone an arthroscopic partial medial meniscectomy within the previous 3 to 12 months will be recruited and randomly assigned to a neuromuscular exercise or control group using concealed allocation. The neuromuscular exercise group will attend 8 supervised exercise sessions with a physiotherapist and will perform 6 exercises at home, at least 3 times per week for 12 weeks. The control group will not receive the neuromuscular training program. Blinded assessment will be performed at baseline and immediately following the 12-week intervention. The primary outcomes are change in the peak external knee adduction moment measured by 3-dimensional analysis during normal paced walking and one-leg rise. Secondary outcomes include the change in peak external knee adduction moment during fast pace walking and one-leg hop and change in the knee adduction moment impulse during walking, one-leg rise and one-leg hop, knee and hip muscle strength, electromyographic muscle activation patterns, objective measures of physical function, as well as self-reported measures of physical function and symptoms and additional biomechanical parameters.

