Exercise may be an effective strategy to reduce the greater medial knee joint load distribution observed post-APM. Exercise is recommended as part of rehabilitation post-meniscal surgery [29] and is also an attractive rehabilitation option considering that it is relatively safe, is a patient-driven strategy that can facilitate long-term self-management, is inexpensive and is clinically advocated in knee OA management [30,31]. There is limited evidence as to the effects of different exercise types on knee joint loading. Studies have examined the effects of knee and hip muscle strengthening [32-34] on medial knee joint loading in older patients with established symptomatic and radiographic knee OA. Despite improving OA-associated symptoms, no change in medial knee joint loading was found during walking with the tested strengthening programs [33,34]. However, some pilot evidence suggests that neuromuscular exercise may reduce loading across the knee joint in people with and without knee OA during more functionally challenging tasks than walking [35,36].

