Neuromuscular training is a broad term used to incorporate many components of exercise training including: balance, perturbation, agility, plyometrics, strength and endurance [37,38]. Furthermore, neuromuscular training programs are designed with various aims: to prevent sports injuries in young athletes [39], to rehabilitate individuals post-sport related injuries [40] and more recently to prevent OA progression [37]. Therefore it is important to acknowledge that a vast array of exercises and intensities are considered neuromuscular in nature. However, regardless of the target population or aim of the training program, a common feature of neuromuscular training is the use of functional weight-bearing exercise positions. Physiologically, neuromuscular training aims to enhance the unconscious motor response by calling upon both afferent signal and central mechanisms responsible for dynamic control [41]. A randomised controlled trial (RCT) reported that following a 4-month neuromuscular training program, participants post-APM improved one-leg hop for distance and improved self-reported outcomes [17,42]. Importantly, this RCT also found improved cartilage quality as indicated by the GAG content on MRI following the neuromuscular exercise program [43]. Neuromuscular training has been found to reduce external abduction knee loads in young healthy females while landing from a jump [35] adding support to the premise that neuromuscular exercise can alter frontal plane moments. Of particular relevance to the current study is evidence that peak KAM can be reduced with neuromuscular exercise in middle-aged individuals with moderate levels of knee OA [36]. This uncontrolled pilot study included 13 individuals and found a 14% reduction in peak KAM during a one-leg rise task with no difference in peak KAM during walking following the 8-week training period. Despite the difference in the purposes of the neuromuscular exercise training programs [35,36], these findings from healthy and OA cohorts suggest that neuromuscular training has potential to reduce frontal plane knee moments. Furthermore, these studies suggest that potential alterations in knee joint load distribution appear to be detected during more challenging motor tasks following neuromuscular training. This hypothesis is further supported by recent cross-sectional evidence in APM individuals describing altered neuromuscular function during a forward lunge [44] that were not detected during stair descent when comparing the operated and non-operated legs [45].

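### The 80% power claim names no task, so it cannot be assigned to either of the two primary peak KAM outcomes as written, nor assumed to hold for both

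*Protocol article*

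**What the plan says.** The Abstract states: "The primary outcomes are change in the peak external knee adduction moment measured by 3-dimensional analysis during normal paced walking and one-leg rise". The objectives, the primary hypothesis and Table 2 agree. Table 2 lists "Peak external knee adduction moment during stance" as the primary measure, once for normal-pace walking and once for one-leg rise.

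The Sample size section opens with an assurance covering peak KAM and KAM impulse in general: "A sample size of 62 participants ensures adequate power to detect significant changes in the external peak KAM and KAM impulse after the 12-week study". For peak KAM it then gives this chain of inputs:

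- Evidence for an effect: "a 14% reduction in peak KAM has been reported during one-leg rise in an uncontrolled study of people with knee OA". From this, and from a link to progression risk, a reduction of at least 10% is called feasible and possibly clinically meaningful.
- Absolute difference: about 0.2 Nm/(BWxHT)%, as 10% of the group's earlier post-meniscectomy data (reference 65). No task is named.
- Variability: "Cautious estimates of the standard deviation of change scores are 0.3 Nm/(BWxHT)%, based on knee OA data from our laboratory investigating conservative treatments for knee" (osteoarthritis; reference 33). No task is named.
- Result: 27 per group for 80% power, two-sided 5%, and 31 per group after attrition.

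Two statements in the Background bear on these inputs. On the strengthening trials, including reference 33: "no change in medial knee joint loading was found during walking with the tested strengthening programs [33,34]". On the pilot that supplies the 14%: it "found a 14% reduction in peak KAM during a one-leg rise task with no difference in peak KAM during walking" after the 8-week programme.

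**The concern.** Peak KAM in walking and peak KAM in one-leg rise are different measurements, each with its own mean, its own variability of change and its own plausible response to training. The protocol accepts this: the Background says that effects seem to show up in the more demanding tasks, and the Discussion justifies the two outcomes on different grounds. Walking is chosen because its KAM is raised after meniscectomy and is linked to progression. One-leg rise is chosen because the pilot suggests that it can be changed.

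The power statement merges the two. It cites the pilot's favourable one-leg-rise result, leaves out the same pilot's walking result, takes its variability from a study reported for walking, and presents the outcome as power for peak KAM as such. A reader will take 80% to apply to each primary outcome and will treat a null result on either as informative. The printed inputs do not justify that for both.

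**Working it through.** **1. Which task each input belongs to**

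| Input | Value | Source given | Task stated in the Sample size section | Task indicated elsewhere |
|---|---|---|---|---|
| Evidence for an effect | 14% | uncontrolled pilot, 13 people with knee OA (reference 36) | one-leg rise | Background: no difference in walking |
| Planned effect | 10% | argued from the 14% and from progression risk (reference 25) | none | Discussion cites reference 25 for walking |
| Absolute difference | about 0.2 | post-meniscectomy data (reference 65) | none | none |
| SD of change | 0.3 | knee OA data (reference 33) | none | Background: walking |

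The implied mean is 0.2 / 0.10 = 2.0 Nm/(BWxHT)%. No row gives a mean or SD of change that is labelled as one-leg rise.

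**2. The plan's own figure**

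For two means, n per group = 2 × (1.960 + 0.842)² × (SD / difference)².

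- Peak KAM: 2 × 7.849 × (0.3 / 0.2)² = 35.3, so 36 per group (37 by the noncentral t).
- KAM impulse: 2 × 7.849 × (0.10 / 0.09)² = 19.4, so 20 per group (21 by the noncentral t).

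The stated 27 follows from neither pair. It can be reached for peak KAM in ways that the protocol does not state: an unrounded difference of 0.23, an SD of 0.26, or a gain from baseline adjustment. For the last, the variance factor is (1 + ρ)/2. With an assumed baseline–follow-up correlation of 0.5, the effective SD is 0.3 × √0.75 = 0.26, which gives 27.

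**3. Power for whichever task the 0.2 and 0.3 describe**

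The standardised difference is 0.2 / 0.3 = 0.667. With 27 per group the noncentrality is 0.667 × √(27/2) = 2.45. Power is 69% by the normal approximation and 67% by the t-test. With all 31 per group the t-test gives 73%. The difference detectable with 80% power at 27 per group is 0.777 × 0.3 = 0.23, or about 12% of 2.0.

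**4. The other primary outcome (illustrative only)**

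The protocol gives no input labelled as one-leg rise. If one borrows the 0.2 difference, which need not be 10% of the one-leg-rise mean, and assumes a range of SDs, an unadjusted t-test with 27 per group gives:

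| Assumed SD of change | Power |
|---|---|
| 0.26 | 79% |
| 0.30 | 67% |
| 0.35 | 54% |
| 0.40 | 44% |
| 0.50 | 30% |

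These are not estimates for this trial. They show only that power depends heavily on a figure the protocol does not give.

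**The case against.** The best defence is that the calculation may be coherent for one outcome. The effect entered is not the pilot's 14% but 10% of the mean in reference 65. If that mean comes from walking, then 0.2 and 0.3 may both be on the walking scale and the calculation describes the walking outcome. That is possible. It is why the documents do not support a stronger reading that a reader might infer: that a one-leg-rise effect was paired with a walking SD, so that the power belongs to neither outcome. The task in reference 65 is not given, and the walking label on the 0.3 is an inference from the Background.

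The 10% also has a second basis. The protocol calls it potentially meaningful because of progression risk, and a trial may be powered on a meaningful difference that no pilot has shown. The pilot was small, uncontrolled, shorter (8 weeks against 12) and in a different population, so its walking result is weak evidence of no effect. This stands, and it means the lack of a walking change in the pilot is a matter for disclosure, not proof that the target is wrong.

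Third, the 67% is not a measure of the task problem. It arises because 27 does not follow from 0.2 and 0.3, which is a separate arithmetic fault, and it ignores the planned adjustment for baseline. That also stands. The figure matters here only because the claim, once limited to one task, has to be restated from its inputs.

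None of this rescues a claim for both outcomes. If the inputs are walking inputs, one-leg rise has no stated power basis.

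**Conclusion.** The point holds in this form: the 80% power is claimed for a peak KAM without a task, cannot be assigned to either primary outcome from what is printed, and cannot be assumed to hold for both. This is more than condensed reporting, because the article prints the whole chain of inputs and draws an assurance of adequate power that the chain does not deliver.

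For the outcome that the 0.2 and 0.3 describe, power is about 67% at 27 per group. This assumes an unadjusted two-sample t-test, a two-sided 5% level and the rounded inputs as printed. An explicit baseline-adjustment gain could raise it to about 80%: a correlation of 0.5 gives 81% by the normal approximation, but 0.9 gives only 71%. For the other primary outcome no figure can be computed.

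The documents do not show that the trial is underpowered on one-leg rise, that a 10% change in walking is implausible, or that the inputs were certainly drawn from different tasks.

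**What to change.** In the Sample size section:

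1. State the task behind the 0.2 (reference 65) and behind the 0.3 (reference 33). If they are the same task, limit the power claim to that task and present it as power for a 10% difference considered meaningful. If they are not, replace one so that they match.
2. Say that the pilot behind the 14% saw no change in walking.
3. Restate the power for that outcome from the printed inputs: about 67% at 27 per group, unless a gain from baseline adjustment is stated with its assumed correlation and justified.
4. Give the other primary outcome its own power or detectable-difference statement, from its own mean and SD of change. If these are not available, state that the trial is not powered on that outcome. Any range built on assumed SDs should be labelled illustrative.
5. Replace the opening assurance of adequate power with wording limited to what items 1 to 4 support.

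The cost is a rewritten section and one further calculation. Enrolment and conduct are unchanged. The downside is a less favourable stated power, claimed for one primary outcome unless inputs for the second can be supplied.

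### On the protocol's own inputs, 80% power for peak KAM, the primary outcome, needs 37 per group; the stated 27 gives about 67%

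*Protocol article*

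**What the plan says.** The Sample size section opens with the claim that "A sample size of 62 participants ensures adequate power to detect significant changes in the external peak KAM and KAM impulse". For peak KAM it says that "a 10% reduction equates to an absolute change of approximately 0.2 Nm/(BWxHT" (in % units) and "Cautious estimates of the standard deviation of change scores are 0.3 Nm/(BWxHT" (same units). It adds: "We anticipate that the peak KAM will remain unchanged in our control group participants". The between-group difference in change is therefore the full 0.2.

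For KAM impulse, "a 10% reduction equates to an absolute change of approximately 0.09 Nm.s/(BWxHT" and "Estimates of the standard deviation of change scores are 0.10 Nm.s/(BWxHT" (again in % units), also with no change expected in controls.

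From these it concludes that "a total of 27 participants per group is required to detect our anticipated changes in peak KAM and KAM impulse", for a between-group comparison with 80% power, a two-sided test and alpha 0.05, using the SDs just given. Recruitment is set at 31 per group to allow for 15% attrition.

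The Abstract and Table 2 make peak KAM (normal-pace walking and one-leg rise) primary and KAM impulse secondary. The Data and statistical analysis section plans a regression of change adjusted for baseline value and sex, with all tests two-tailed at 5%.

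**The concern.** The section prints everything a two-sample calculation needs: difference, SD of change, alpha, sidedness, power and equal groups. The printed result does not follow from these inputs for the outcome that matters most. A standardised difference of 0.667 calls for clearly more than 27 per group, and 0.90 for clearly fewer, so one figure of 27 cannot be the 80% requirement for both.

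The risk lies in how the trial is read. If peak KAM shows no significant difference, readers will take the stated 80% power as grounds for concluding that the program does not reduce medial load by the targeted 10%. At the stated inputs, in an unadjusted test, the chance of missing that effect is about one in three, not one in five.

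**Working it through.** **Inputs, all from the Sample size section**

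| | Peak KAM (primary) | KAM impulse (secondary) |
|---|---|---|
| Difference in change | 0.2 | 0.09 |
| SD of change | 0.3 | 0.10 |
| Standardised difference d | 0.2/0.3 = 0.667 | 0.09/0.10 = 0.90 |

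Two-sided alpha 0.05, power 80%, equal allocation.

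**Step 1: try to reproduce 27.** The normal approximation is n per group = 2(1.96 + 0.8416)² / d².

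- Peak KAM: 2 × 7.849 / 0.4444 = 35.3, so 36. The t-test (noncentral t) gives 36.3, so **37**.
- KAM impulse: 2 × 7.849 / 0.81 = 19.4, so 20. The t-test gives 20.4, so **21**.

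Neither is 27.

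**Step 2: power at the planned sizes (t-test)**

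| Analysed per group | Peak KAM |
|---|---|
| 26 (31 × 0.85 = 26.35) | 65.4% |
| 27 | 67.2% |
| 31 (no attrition) | 73.3% |
| 37 | 80.8% |

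The normal approximation gives 68.8% at 27, so the conclusion does not depend on the formula. KAM impulse has 90.1% power at 27.

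**Step 3: what 27 per group can detect.** At 80% power the detectable d is 0.777. With SD 0.3 that is a difference of 0.777 × 0.3 = 0.233. The article equates a 10% reduction with 0.2, which implies a mean of about 2.0, so 0.233 is 11.7% of that mean.

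**Step 4: routes that might lead to 27**

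- *One-sided test at 0.05:* 29 per group by t-test, 28 by normal approximation. This contradicts the stated two-sided test.
- *Unrounded inputs:* with SD 0.30, a difference of 0.235 needs 26.6, so 27. With a difference of 0.2, the SD would have to be 0.2/0.777 = 0.257.
- *Baseline adjustment:* the residual SD would have to fall from 0.3 to 0.257. The correlation between baseline and change would then need a magnitude of √(1 − (0.2574/0.3)²) = 0.51. With equal baseline and follow-up variances, that is a baseline–follow-up correlation of 2 × (0.2574/0.3)² − 1 = 0.47. With the change SD held at 0.3, a higher correlation helps less: at 0.7, 0.8 and 0.9 the need is 32, 33 and 35 per group, and power at 27 is 74%, 72% and 69%.
- *KAM impulse at 90% power:* 26.9, so 27. This matches numerically, but it is a secondary outcome and not the stated power.

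The article states none of the conditions these routes require.

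**The case against.** The strongest defence is rounding. The difference is given as approximate, and both peak KAM inputs carry one significant figure. Values that round to 0.2 and 0.3 span 0.15–0.25 and 0.25–0.35, for which the required number runs from about 17 to about 87 per group. Small shifts suffice: 0.21 with SD 0.27 needs 26.9, and 0.22 with SD 0.28 needs 26.4. If the unrounded 10% change were 0.233, the implied mean would be 2.33 and the detectable change would be exactly 10%. The planned regression also adjusts for baseline and sex, so its power should be somewhat above that of an unadjusted test, and the authors call their SD cautious. Finally, an article condenses a fuller protocol that may hold the missing inputs.

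Part of this stands. The origin of 27 is unknown, and the 67%, the one-in-three error and the 11.7% are conditional on 0.2 and 0.3 taken as printed and on an unadjusted test.

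It does not rescue the statement. Rounding works in both directions: 0.15 with SD 0.30 needs 64 per group. The section says the calculation used the SDs as given, so a smaller SD would contradict it. Baseline adjustment reaches 80% at 27 only if the baseline–follow-up correlation is about 0.47 or lower, and the section neither mentions adjustment nor gives a correlation. Nor is this a complaint about omitted detail: a complete set of inputs is printed beside a result that does not follow from them.

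The section also does not say which task the 0.2 and 0.3 describe. The cited 14% effect is for one-leg rise, and the Background reports the same pilot "with no difference in peak KAM during walking following the 8-week training period". That is a matter of detail, and the arithmetic does not rest on it.

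**Conclusion.** The concern holds. At the stated difference of 0.2 and change SD of 0.3, with a two-sided 5% two-sample t-test, 80% power needs 37 per group (36 by normal approximation). The stated 27 is 10 short and gives 67% power. Even complete follow-up of all 31 per group gives only 73%. The claim that 62 participants provide adequate power is therefore unsupported for peak KAM, the primary outcome, though sound for KAM impulse. Baseline adjustment would raise the peak KAM figure somewhat, to 69–74% for baseline–follow-up correlations of 0.9 to 0.7, but that range still falls short of 80%.

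**What to change.** Rewrite the Sample size section in one of two ways.

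1. If 27 came from unrounded inputs or from the precision gained by baseline adjustment, state those inputs and show that they reproduce 27. Examples are a difference near 0.235 with SD 0.30, or a baseline–change correlation of magnitude about 0.51.
2. Otherwise, state that 27 analysed per group gives about 67% power for a difference of 0.2 with SD 0.3, or 80% power for about 0.23 (11.7% of the implied mean of 2.0). Withdraw the claim of adequate power for peak KAM and keep it for KAM impulse.

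In either case it would help to say which task the 0.2 and 0.3 refer to.

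The cost is a reworded paragraph and, under the second option, a less favourable stated power. No extra participants are needed. Keeping 80% power at the stated inputs would be a different decision: 37/(1 − 0.15) = 43.5, so 44 per group or 88 in total.
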